### Sample size

The sample size has been calculated according to the primary interest variable, TB BMD (of cyclists (aged 15.5 years) [39] in order to achieve 90% of statistical power to detect differences in the contrast of the null hypothesis H0: μ1 = μ2 through bilateral student t, difference between two dependent means (matched pairs). Taking into account a significance level of 5% and assuming that the mean of the reference group 1.133 units (SD = 0.127) and the mean of the experimental group is 1.002 units (SD = 0.093), it will be necessary to include 9 participants in the reference group and 9 participants in the experimental group, totalling 18 participants. It is known that the number of participants to recruit depends also on potential withdrawals [or could use drop-outs]: n’ = n/(1-p), so that if the withdrawals were 40% the number of participants to be recruited would be n’ = 9/(1–0.4) = 15 in each group (e.g. 15 INT cyclists + 15 CON cyclists = 30 cyclists). Therefore, cyclists (n = 30), footballers (n = 30), swimmers (n = 30) and controls (n = 15) will be recruited, yielding a total N = 105.

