PRO-BONE will employ different and well known technological devices and methods such as DXA, BodPod, imaging bone ultrasonometer and triaxial accelerometers among others. In addition, the PJT will include a progression in intensity with ankle weights to maximize the potential to augment bone. PRO-BONE is timely as there is a lack of studies analysing the effects of PJT on bone health during the crucial this period of life. It represents a golden opportunity to measure how a simple, feasible and inexpensive PJT is associated with bone health in adolescents engaged in different sports. It will also show if the effect of this intervention differs between sports, expecting a greater effect in cyclists and swimmers than footballers. In addition, PRO-BONE will allow us to compare within each group and investigate changes in body composition in groups doing the PJT plus training vs groups only training. Finally, PRO-BONE will examine whether PJT has any additional effect on footballers. Football is considered one of the most osteogenic sports, but this type of intervention has not yet been studied.

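### Footballers are given the sample size derived from a cyclist difference, although the protocol expects a smaller jump-training effect in football; the implied 90% power does not carry over if variability is similar

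*Protocol article*

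**What the plan says.** The Sample size section of the protocol article bases its calculation on one outcome in one sport: "The sample size has been calculated according to the primary interest variable, TB BMD (of cyclists (aged 15.5 years". The stated aim is "in order to achieve 90% of statistical power to detect differences", with a two-sided 5% level and a t test described as "through bilateral student t, difference between two dependent means (matched pairs". The inputs are "the mean of the reference group 1.133 units (SD = 0.127" and, for the experimental group, 1.002 (SD 0.093). The result is 9 per group, raised to 15 per group for 40% withdrawals, with the two cyclist sub-groups as the worked example. The section then concludes: "Therefore, cyclists (n = 30), footballers (n = 30), swimmers (n = 30) and controls (n = 15) will be recruited". Nothing specific to football enters the calculation.

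The second objective names footballers, cyclists and swimmers as the boys in whom the jump programme is to be assessed. The Discussion says the trial will show whether the effect differs between sports, "expecting a greater effect in cyclists and swimmers than footballers". It also makes football a question of its own: "PRO-BONE will examine whether PJT has any additional effect on footballers".

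**The concern.** With the number of boys, the significance level, the test and the variability held fixed, power falls as the true effect falls. The protocol uses one difference to set the number in every sport, and elsewhere says it expects the effect in one of those sports to be smaller. A reader of the Sample size section would take the 30 footballers to be the number that delivers 90% power for the football comparison, because no other basis for that number is given.

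Football is one of three randomised comparisons and, on the protocol's own expectation, the one with the smallest effect. If its power is well below that implied, a non-significant football result beside a significant cyclist result would say little about whether the programme adds anything in an osteogenic sport.

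**Working it through.** **Inputs (Sample size section).** Difference 1.133 − 1.002 = 0.131 g/cm²; SDs 0.127 and 0.093; two-sided 5%; target power 90%; 9 evaluable per group; 40% withdrawals. No correlation is given for the matched pairs, and no size is given for the football effect.

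**Step 1: reproduce the protocol's figure.** For matched pairs, the SD of the difference is √(0.127² + 0.093² − 2ρ × 0.127 × 0.093). With the exact (noncentral t) calculation:

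- ρ = 0 needs 18 pairs;
- ρ = 0.5 needs 11 pairs;
- 9 pairs is returned for ρ from about 0.575 to 0.645.

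So 9 is reproducible, with an unstated correlation of roughly 0.6. The withdrawal step is right: 9/(1 − 0.4) = 15.

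**Step 2: calibrate in the protocol's favour.** Set ρ = 0.575, so that 9 pairs give exactly 90% power at 0.131. The SD of the difference is then 0.1059 and the standardised difference is 0.131/0.1059 = 1.237.

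**Step 3: the same comparison as two independent groups.** The boys in each sport are randomised to two separate sub-groups. The pooled SD is √((0.127² + 0.093²)/2) = 0.1113, so the standardised difference is 0.131/0.1113 = 1.177. A two-sample t test then needs 17 per arm for 90% power.

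**Step 4: power at smaller effects.** The fractions are assumptions, because the protocol gives only the direction. The noncentrality is (difference/0.1059) × √n for pairs and (difference/0.1113) × √(n/2) for independent arms. SDs and correlation are kept at the cyclist values.

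| Share of 0.131 | Difference (g/cm²) | 9 pairs | 15 pairs | 9 per arm, independent | 15 per arm, independent |
|---|---|---|---|---|---|
| 100% | 0.131 | 90% | 99% | 65% | 87.5% |
| 90% | 0.118 | 83% | 98% | 56% | 80% |
| 75% | 0.098 | 69% | 92% | 42% | 65% |
| 50% | 0.066 | 37% | 61% | 22% | 34% |
| 25% | 0.033 | 13% | 20% | 9% | 12% |

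The columns for 9 are the design case, because the protocol recruits 15 to cover 40% loss. The columns for 15 assume that nobody withdraws.

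**Step 5: detectable difference.** Solving the same power function for 90% with independent arms gives about 0.181 g/cm² with 9 per arm and 0.137 g/cm² with 15 per arm. Both exceed 0.131.

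**The case against.** Four points on the other side have substance.

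- *The protocol does not claim 90% power for football in words.* This is correct. The 90% is attached to a calculation on cyclist data, and what is carried over is a number of boys. One common number per sport is also a normal and convenient choice. But the cyclist sub-groups are offered as an example, and the football number is presented as a consequence of the calculation, so the power is implied.
- *The 0.131 is not shown to be a jump-training effect.* This also stands. The experimental mean is the lower of the two, whereas the programme is expected to raise bone mass, so the inputs look more like a cross-sectional group difference. The conflict with the Discussion is therefore conditional on reading 0.131 as the effect assumed for cyclists. If it is not, the 90% is unsupported for cyclists too, which does not help football.
- *Football boys may vary less.* A reader might infer that 15 per sub-group cannot possibly give footballers 90% power. The documents do not support that. They give no football SD or correlation, and 75% of the effect with an SD of the difference also 25% smaller would restore 90%. Rounding leaves some slack as well: at ρ = 0.645, 9 pairs give about 94% at 0.131, and about 92% of the effect still reaches 90%.
- *Full retention helps.* On the matched-pairs basis, 15 retained pairs give 92% at three quarters of the effect. They give only 61% at half, and the protocol itself plans for 9.

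How a non-significant football result will be worded is a reporting matter that an analysis plan may settle. The protocol nowhere says that it would be read as no effect.

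**Conclusion.** The point holds in a conditional form. The number of footballers rests on a single cyclist difference, while the protocol expects a smaller jump-training effect in football. If 0.131 g/cm² is the effect assumed for cyclists, and football SDs and correlation are similar, the implied 90% is not the power of the football comparison. The direction is clear for any materially smaller effect. The size is not fixed by the documents: with 9 evaluable per sub-group, across assumed fractions of 75% to 25%, power runs from about 69% down to 13% for matched pairs and from 42% down to 9% for independent arms.

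This is a weakness in a sample-size assumption. It is not an arithmetic error: the step from 9 to 15 is right, and 9 can be reproduced under matched pairs. Nor does it follow that the 90% is sound for cyclists, since two independent sub-groups of 9 give about 65% at 0.131.

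**What to change.** In the Sample size section, state that the 90% applies only to a difference of 0.131 g/cm² under the matched-pairs assumption, and that it is not a power for the football comparison. For football, give either the power over a range of effects below 0.131 or the detectable difference, at the 9 evaluable and 15 recruited per sub-group already planned. Use a test that fits two independent randomised sub-groups, and state the SDs assumed. Apply the same check to cyclists, so that the 90% is not left standing there by default.

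In the Discussion, present the football comparison as an estimated difference with its 95% confidence interval.

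The change is to wording and one added calculation. It needs no extra participants, visits or measurements. The cost is a less favourable stated power, for football and probably for cyclists as well.

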### Recruitment of the participants

Participants and parents/guardians will be contacted via advert flyers, posters and social media to participate in this study and by contacting sport clubs and schools from the South West of England. Where possible, a meeting will be held to explain the project as well as to answer any questions. At the end of this meeting, consent/assent forms and information sheets will be given out and participants and parents/guardians will have 15 days to return the consent/assent forms. After these 15 days, a reminder (phone call or email) will be provided to those not sending the consent/assent to check if they wish to participate. Seven more days will be given to those that agreed to participate and in the 2^nd^ reminder, they will be asked to send the interest and consent/assent forms signed.

Participants will be screened for eligibility, based on the inclusion/exclusion criteria outlined below, by a member of the research team depending on the information provided in the interest form. If eligible, the baseline assessment will be scheduled for the participant. All participants and parents involved in this project will be carefully informed about the risks and benefits of the study and will be required to sign the approved assent and consent forms before their visit to the laboratory at the Children’s Health and Exercise Research Centre (CHERC, University of Exeter).

### Inclusion and exclusion criteria

Inclusion criteria include: 1) Males 12–14 years old, engaged (≥3 h/week) in osteogenic (football) and/or non-osteogenic (swimming and cycling) sports in the last 3 years or more; 2) Male adolescents 12–14 years old not engaged in any of these sports (≥3 h/week) in the last 3 or more years (control group).

Exclusion criteria include: 1) participation in another clinical trial; 2) any acute infection lasting until < 1 week before inclusion; 3) medical history of diseases or medications affecting bone metabolism or the presence of an injury (before inclusion) that may affect participation in their respective sports and/or any variable considered in the present study (i.e. doing the PJT); 4) non-Caucasian participants. The latter is included since there are differences in body composition (bone, fat and fat-free mass) and biochemical markers (i.e. osteocalcin) between ethnic groups [62].

### Ethics approval

The methods and procedures of the PRO-BONE study have been checked and approved by: the Ethics Review Sector of Directorate-General of Research (European Commission, ref. number 618496), the Sport and Health Sciences Ethics Committee (University of Exeter, ref. number 2014/766) and the National Research Ethics Service Committee (NRES Committee South West – Cornwall & Plymouth, ref. number 14/SW/0060). All data and information obtained will be confidential and access to database will be restricted to the researchers of the study. All measurements will be carried out by qualified and experienced researchers that will undergo a Disclosure and Barring Service check for approval to work with young people.

### Study protocol and measurements

#### Body composition

##### Anthropometry

Stature (cm), seated height (cm) and body mass (kg) will be measured by using a stadiometer (Harpenden, Holtain Ltd, Crymych, UK; precision 0.1 cm; range 60–210 cm), a sitting height table (Harpenden, Holtain Ltd., Crymych, UK; precision 0.1 cm; range 32–109 cm) and an electronic scale (Seca 877, Seca Ltd, Birmingham, UK; precision 100 g; range 2–200 kg) respectively. Body mass index (BMI) will be calculated as body mass (kg) divided by the height (m) squared.

Waist circumference will measured at the midpoint between the lowest rib cage and the top of the iliac crest. Hip circumference will be measured around the widest portion of the buttocks. All measurements will be undertaken by the same trained researcher using the type Seca 201 measuring tape (Seca Ltd, Birmingham, UK; precision 0.1 cm; range 0–205 cm). All anthropometrical measurements will be performed three times and the mean will be calculated. Pubertal maturation will be self-reported by the participants during each visit using adapted drawings of the five stages (Tanner) of pubertal hair development [63].

##### Dual-energy x-ray absorptiometry

Dual-energy x-ray absorptiometry scanner (GE Lunar Healthcare Corp., Madison, WI, USA) will be used to scan participants at four sites due to the evidence of site specific impact of sports participation [64-66]: 1) LS (mean of L1-L4), 2) right hip, 3) left hip, 4) TB. The DXA equipment will be calibrated at the start of each testing day by using a LS phantom as recommended by the manufacturer. The body will be segmented in accordance to standard procedures to evaluate regional bone mass and fat distribution. The scan modes will be automatically selected by the scanner software (standard or thick). All DXA scans and analyses will be performed using the GE enCORE software (2006, version 14.10.022).

Participants will be asked to remain still and they will be scanned in the supine position. The BMC (g) and BMD (g/cm^2^) with aged-matched Z-scores and age-matched % will be obtained. For LS regions area (cm^2^), width (cm) and height (cm) will be recorded and for TB regions, fat mass (g), lean mass (kg) and body fat (% and kg) will be obtained. Information about hip strength index, fat mass ratios (trunk/total, legs/total, arms and legs/trunk), android and gynoid regions will also be obtained and have been previously validated in adolescents [67].

This technique uses ionizing radiation that raises ethical issues particularly for child participants. However, this technique uses a minimal radiation dose (similar to spending a day outside in the sunshine), and has been widely used for research purposes with child participants worldwide. The estimated lifetime risks of using GE Lunar Prodigy DXA measurements in the paediatric population was found to be negligible [68].

##### Air displacement plethysmography

Body volume will be measured with BodPod (Body Composition System, Life Measurement Instruments, Concord, California, USA) as it can effectively predict visceral adipose tissue in children [69] and determine the changes of body fat percentage over time [70]. Two measurements will be performed and if there is a difference of more than 150 mL in body volume, a third measurement will be taken. The equipment will be calibrated at the commencement of each testing day following the manufacturer’s guidelines and using a cylinder of specific volume (49.887 L). Participants will wear clothing according to the manufacturer’s recommendation (a swimsuit and a swim cap) to rule out air trapped in clothes and hair. Participants will be weighed on the BodPod calibrated digital scale and then will enter into the BodPod chamber. During the measurements participants will be asked to remain in a seated position and to breathe normally. A mean value for body volume will be obtained following the manufacturer’s recommendations [71] and this value will be integrated into the calculation of lung volume. Percentage of TB fat mass will be calculated using the equation reported by Siri [72,73].

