## Background

Osteoporosis is a common skeletal disease associated with high morbidity and mortality [1]. Approximately 2.7 million European men and women suffer an osteoporotic fracture every year [2]. The economic burden of osteoporosis in Europe is higher than most types of cancer (except lung cancer), or chronic cardiorespiratory diseases [2,3] and represents a direct annual cost of ~ €31.7 billion to health care and social services [1]. In order to improve the outcome for osteoporosis, primary prevention remains the most important policy action in public health. Although contested [4], it is generally accepted that acquiring a high bone mass during childhood and adolescence is a key determinant of adult skeletal health [5-7]. Approximately 60% of osteoporotic cases in adult life are related to low bone mineral content (BMC) in adolescence with up to 50% of total body (TB) bone mass achieved during this period of life [8,9]. Peak bone mass attainment typically occurs between the second and third decade of life, with 80-90% acquired by late adolescence, although this is skeletal site dependent [6,10]. Although bone mass is ~ 60-80% genetically determined [11], there are other factors strongly related with bone mass development. Environmental and lifestyle factors such as physical activity (PA) [12] and nutrition, i.e. calcium intake [13] and vitamin D [14], are known to have important osteogenic effects and have been the key focus in several interventions.

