### Sport participation and bone health

It has been shown that sport participation is crucial for healthy bone development, however not all sports have a positive influence on the skeletal mass. According to their characteristics, sports can be described as osteogenic (weight-bearing exercise) and non-osteogenic (non weight-bearing exercise). Apart from numerous health benefits [26], football is considered as an osteogenic sport both in childhood and adolescence as bone mass is augmented [27-30]. In contrast, sports such as cycling [31-40] or swimming [41-46] are associated with no change or a reduction in bone mass when compared to controls. This could be a barrier for obtaining a high peak bone mass which may compromise future bone health [40,41,46,47].

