### Plyometric exercise intervention to increase bone health

To achieve the benefits of exercise and gain acceptance, PA models must be effective, simple to administer, feasible, inexpensive, short in duration and possible to perform at any location (i.e. at home, at the sports centre). Plyometric jump training (PJT) may be a judicious choice and experimental studies using animal models have repeatedly shown that short, discrete bouts of exercise interspersed with rest periods is more effective than a single longer bout of exercise for improving bone mass and strength [48].

Research in early puberty has shown that a novel and easily implemented 8-month PJT (Bounce at the Bell; ~3 min/day) enhanced bone mass at the weight bearing proximal femur [49]. Mackelvie et al. showed that a 7-month jumping intervention (10 min, 3 times/week) was associated with more bone at the FN and lumbar spine (LS) in early pubertal girls [50], and these results were maintained after 2 years [51]. In addition, prepubertal Asian and Caucasian boys of average or low body mass index (BMI) augmented bone mineral accrual at several regions after a 7-month jumping intervention (10 min, 3 times/week). However, there are a lack of studies analysing the effect of PJT in the adolescent population, which is crucial as adolescence is the period associated with the greatest increments in BMC and BMD [52]. In addition, this has not been studied in adolescents engaged in different sports (osteogenic vs. non osteogenic), which is important to examine if peak bone mass during adolescence may be maximized and therefore reduce the risk for developing osteoporosis in adulthood.

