## Methods/Design

### Study design

PRO-BONE is a longitudinal design and involves four cohorts of males aged 12–14 years at the beginning of the study. These four cohorts consist of footballers, cyclists, swimmers and controls that will be followed over a period of 33 months. The timeline of the PRO-BONE study can be seen in Figure 1.

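### BodPod percentage fat by Siri's equation carries a bone- and maturity-dependent bias in change over time and in between-sport comparisons

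*Protocol article*

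**What the plan says.** The section Air displacement plethysmography fixes one conversion from body density to fat for every boy, visit and group: "Percentage of TB fat mass will be calculated using the equation reported by Siri [72,73". No version adjusted for age, maturity or mineral is named. The same section gives as one reason for choosing the device that it can "determine the changes of body fat percentage over time".

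The rest of the article describes a population in which bone is expected to move:

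- Study design: "four cohorts of males aged 12–14 years at the beginning of the study", "followed over a period of 33 months".
- Background, on adolescence: "with up to 50% of total body (TB) bone mass achieved during this period of life".
- Sport participation and bone health: football is said to augment bone, whereas cycling and swimming "are associated with no change or a reduction in bone mass when compared to controls".

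Body fat is measured in three ways: DXA, BodPod and bioelectrical impedance. The article does not say which is the main one. The Discussion promises a comparison of body composition changes between jump-training and sport-only groups. The sample size is based on total-body BMD, which comes from DXA.

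**The concern.** Siri's equation is a two-component formula. It splits the body into fat and fat-free mass and gives each a fixed density. If the fat-free part is denser than assumed, the formula reports too little fat; if it is less dense, too much. Bone mineral is the densest component of fat-free mass, so a boy whose mineral share rises while his fat stays the same is recorded as having lost fat. Of two boys with equal fat, the one with the larger mineral share is recorded as the leaner.

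The comparisons most exposed are change over the 33 months and football against cycling or swimming, both of which belong to the first objective. The error is systematic, so neither more participants nor repeat readings remove it. With no main fat measure named, a gap between BodPod and DXA that follows bone could be reported as a finding about fat.

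**Working it through.** The article gives no BodPod fat figure, so there is nothing to reproduce. What follows is a sensitivity calculation.

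**Inputs**

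- Assumed, because the article prints no constants: fat density 0.900 and, inside Siri's equation, fat-free density 1.100 (g/mL).
- Assumed: true fat-free density *d* from 1.080 to 1.105, and true fat fraction *f* of 14% or 15%.
- Assumed for the bone-only step: mineral is 4–6% of fat-free mass, mineral density 3.0, baseline *d* = 1.09.
- From Sample size: total-body BMD 1.133 against 1.002, so (1.133 − 1.002)/1.133 = 0.131/1.133 = 11.6%. It is used only as a stand-in for a contrast in mineral.

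**Step 1: what the equation assumes.** Body density D satisfies 1/D = *f*/0.900 + (1 − *f*)/*d*. Setting *d* = 1.100 and solving for *f* gives 100 × 0.9 × 1.1/(1.1 − 0.9) = 495 and 100 × 0.9/(1.1 − 0.9) = 450. Hence Siri % fat = 495/D − 450, and the constant density is built into the coefficients.

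**Step 2: error when *d* is not 1.100.** Substituting gives error = (1 − *f*) × (495/*d* − 450) percentage points. At 15% fat and *d* = 1.090 this is 0.85 × (454.13 − 450) = 3.51.

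| True *d* | Error at 15% fat (points) |
|---|---|
| 1.080 | +7.1 |
| 1.085 | +5.3 |
| 1.090 | +3.5 |
| 1.095 | +1.8 |
| 1.100 | 0 |
| 1.105 | −1.7 |

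The slope is about 3.5 points per 0.01 g/mL. The table shows offsets in level. Bias in a change or a contrast is the difference between two rows.

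**Step 3: the part due to bone alone.** Add mineral to the fat-free mass, hold everything else fixed, recompute Siri, and subtract the small true change in fat fraction. Worked case, 5% mineral share and 5% more mineral, per unit of body mass:

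- Mass: 0.15 + 0.85 × 1.0025 = 1.002125.
- Volume: 0.15/0.9 + 0.85 × (1/1.09 + 0.0025/3.0) = 0.947192.
- Siri: 495 × 0.947192/1.002125 − 450 = 17.87, against 18.51 before, a change of −0.64.
- True change: 100 × 0.15/1.002125 − 15 = −0.03.
- Spurious change: about −0.61.

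| More mineral | Spurious change, mineral share 4% to 6% (points) |
|---|---|
| 2% | −0.2 to −0.3 |
| 5% | −0.5 to −0.7 |
| 11.6% | −1.1 to −1.7 |

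**Step 4: a larger density shift.** At 14% fat, a rise in *d* from 1.083 to 1.092 takes Siri from 20.07% to 16.84%, a fall of 3.2 points with fat unchanged. With the Step 3 assumptions for mineral share and density, bone alone would need the mineral share of fat-free mass to rise by about 20–31% in relative terms to produce this (for example from 5% to about 6.2%).

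**The case against.** Several objections carry weight.

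- **Bone mass is not mineral share.** The article speaks of absolute bone gain. Fat-free density depends on mineral as a proportion of fat-free mass, and lean mass also grows in puberty. The documents give no mineral share, hydration or fat-free density at any age. This stands: the mechanism follows from the equation, but the size, and the direction over time, rest on assumptions.
- **A loss of about 3 points misread from bone.** A reader might infer this from Step 4. The documents do not support it. Most of such a shift would have to come from hydration or other maturational change; bone alone gives the smaller figures in Step 3.
- **Bias in the randomised comparison.** A reader might infer that the jump-training effect on fat is seriously distorted. Allocation is within each sport (Jumping intervention), so maturation bias should balance on average. What remains is bias through the programme's own effect on bone, about 0.2–0.3 points for an assumed 2% effect on mineral.
- **A peripheral variable.** The stated objectives concern bone and its metabolism. Total-body BMD and DXA fat do not use Siri, so it would be wrong to say that the study's bone results are misread as fat. Tracking fat change is a reason given for the device, not a declared endpoint.
- **Unseen references.** Two sources are cited for the equation, and the second might modify it. That cannot be checked, but the method as named is Siri's.

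These points limit the reach and size of the concern without removing it. DXA fat is available at each visit, but the article does not say it takes precedence over BodPod.

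**Conclusion.** The point holds for BodPod percentage fat only. A conversion with constant fat-free density is fixed for boys in puberty and for sports selected because they differ in bone, so change over time and football against cycling or swimming carry a bias that depends on bone and maturity. More mineral relative to lean tissue reads as less fat.

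With Siri's usual constants, the sensitivity at 15% fat is about 3.5 points per 0.01 g/mL. The bone share of that is modest: 0.2–0.7 points for 2–5% more mineral and 1.1–1.7 points for an 11.6% contrast. That contrast is areal BMD from a reference sample of cyclists aged 15.5 years and serves only as a proxy. All of these sizes depend on the assumed densities and mineral share. This is an inexpensive improvement to a supplementary measure and does not threaten the main bone results.

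**What to change.** Choose one of the following and state it before analysis:

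1. Convert BodPod body volume together with same-visit DXA bone mineral in a three-component calculation (fat, mineral, mineral-free lean). This removes the bone part of the bias. It still assumes constant hydration of the lean part, so some maturational bias remains.
2. Replace Siri's constants with fat-free density constants specific to age and sex. This addresses average maturation but not bone differences between sports at the same age.
3. Keep Siri, name DXA percentage fat as the main body-fat measure, and do not interpret change or between-sport differences in Siri percentage fat.

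Body volume and DXA are already planned at each visit, so no measurement is added. The cost is a little extra analysis and, under the first two options, less comparability with studies that report Siri values. Reporting Siri alongside as a secondary figure would preserve that comparability.
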